### Other assessments

Demographic profiles and histories of patients will be recorded at the baseline visit, including sex, age, marital status, education level, smoking and drinking habits, comorbidities, pathological type of gastric cancer, gastric cancer stage, type of resection surgery, chemoradiotherapy regimen, and medication history for the past 3 months.

### Study visits and outcome assessments

The duration of follow-up will be 2 years. Patients will visit at baseline and at 2, 4, 8, 26, 52, 78, and 104 weeks. At each visit, questionnaires and physical examinations will be completed, self-reported AEs will be recorded, and compliance will be assessed. At 8, 26, 52, 78, and 104 weeks, laboratory examinations and electrocardiograms will be performed, and cancer progression will be assessed. A detailed schedule of the trial is presented in Fig. 2.

**Fig. 2 Fig2:**
[figure not shown]
Schedule of the trial process. Abbreviations: *ALT* alanine transaminase, *AST* aspartate aminotransferase, *TBIL* total bilirubin, *DBIL* direct bilirubin, *IBIL* indirect bilirubin, *SCr* serum creatinine, *BUN* blood urea nitrogen, *PT* prothrombin time, *APTT* activated partial thromboplastin time, *TT* thrombin time, *FIB* fibrinogen

### Sample size estimation

This RCT is a superiority trial, and an appropriate formula was used to estimate sample size [24]. Based on the results of our preliminary observational study and expert advice, we assume an α of 0.05, a 1 –β of 0.80, a between-group difference in primary outcome (total SQD scale score) δ of 8.0, a pooled standard deviation of 14.5, and an allowable dropout rate of 20%. The total sample size is expected to be 130 (65 in each group).

## Statistical analysis

Data analysis will be performed with Stata v14.0 (StataCorp LLC, College Station, TX, USA). The main primary outcome analysis will be based on the intention-to-treat data set, where the missing values will not be imputed and the patients who took unscheduled medications will be kept in their original group. We will also perform four sets of sensitivity analyses to test the robustness of the results of the main analyses, including (1) using the per protocol data set; (2) imputing missing data using various methods dependent on the proportion and distribution of the missing data; (3) excluding patients who become aware of the grouping accidentally during the trial, which also aims to estimate the placebo effects; and (4) excluding patients who took unscheduled medications. The analysis of secondary outcomes will be based on the per protocol data set, and the analysis of safety outcomes will be based on the safety data set only, both with no imputation. Interim data analyses will be performed after weeks 8 and 52.

Descriptive analysis will be conducted to explore the means and standard deviations of the continuous variables. We will assess the treatment effects by comparing the mean between-group differences of the continuous endpoints with a normal distribution using the independent *t* test. The skewed continuous variables will be described using medians and interquartile ranges. We will use the Mann-Whitney *U* test to assess the equivalency of the skewed continuous variable distributions. Moreover, we will describe categorical variables through their frequencies and percentages. We will evaluate the between-group differences using Pearson’s chi-square test for the cases with expected counts greater than 5 in more than 20% of cells and greater than 1 in any cell or Fisher’s exact test otherwise. We will perform subgroup analyses stratified by gastric cancer stage and chemoradiotherapy regimen for the primary outcome. We set α = 0.05 as the nominal type I error rate, which will be adjusted for the multiple *t* test using the O’Brien-Fleming group sequential method [25].

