### Outcome measurements

#### Primary outcome

The primary outcome is the change in the total score of the Spleen Qi Deficiency Symptoms Grading and Quantifying scale (SQD scale). The SQD scale is a modified version of the classic scale for assessing the degree of SQD in the Clinical Guideline of New Drugs for Traditional Chinese Medicine [21]. The SQD scale consists of 17 items regarding symptoms of SQD: (1) stomach distension, (2) abdominal distension, (3) physical fatigue and weakness, (4) mental fatigue and taciturnity, (5) loss of appetite, (6) abnormal stools, (7) stomach pain, (8) stomach tightness, (9) abdominal pain, (10) acid reflux, (11) belching, (12) nausea and vomiting, (13) abnormal bowel sounds, (14) powerless defecation, (15) sallow complexion, (16) loss of taste and hypodipsia, and (17) facial and limb edema. Items 1–6 are the main symptoms; the other items are secondary symptoms. The items are assessed for duration (0–3 points, only available for items 1–2 and 7–9), severity (0–3 points, not available for item 13), frequency per day (0–4 points; 0–3 points for item 5), and frequency per week (0–5 points). The total score is the sum of the scores of each item (the main symptoms are scored twice) and ranges from 0 to 292. A higher score indicates a more severe symptom. Compared with the classic scale, we added four items (items 1, 7, 10, and 11), defined the main symptoms according to TCM theory, and assessed each item for duration, severity, and frequency per day and per week rather than only for severity. The details of the SQD scale are presented in Additional file 1.

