### Compliance and withdrawal

To improve patient compliance, we will offer all test samples (HGMX and placebo) and scheduled examinations free of charge, and patients will receive a travel allowance of 100 yuan at each visit. At the recruitment stage, researchers will emphasize the length of the 2-year treatment and follow-up to patients who are willing to join the trial. The patients will be allowed to complete each follow-up within ±3 days of the scheduled date for the weeks 2, 4, and 8 visits and within ±7 days for the weeks 26, 52, 78, and 104 visits. The used packaging bags will be reclaimed to check patients’ compliance.

Patients will be withdrawn from the trial for the following reasons:Cancer progression and restarting of radiotherapy or chemotherapyRecurrence of surgical complicationsContinuous deterioration of SQD symptomsPoor compliance, indicated by the use of less than 80% of the prescribed trial drug or more than two missed visitsActive withdrawal. Patients can actively withdraw from the trial at any time for any reason, and subsequent treatment will not be affected

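### Patients are withdrawn from the trial for reasons tied to the primary outcome, and the unimputed t test labelled intention-to-treat then omits their missing scores, so the primary comparison is open to bias in either direction

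*Protocol article*

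**What the plan says.** All references are to the protocol article.

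- **Primary outcome:** "The primary outcome is the change in the total score of the Spleen Qi Deficiency Symptoms Grading and Quantifying scale (SQD scale"). The scale runs from 0 to 292 and higher is worse. No primary visit is named.
- **Study visits and outcome assessments:** "Patients will visit at baseline and at 2, 4, 8, 26, 52, 78, and 104 weeks".
- **Compliance and withdrawal:** "Patients will be withdrawn from the trial for the following reasons". The reasons are cancer progression with radiotherapy or chemotherapy restarted, recurrent surgical complications, SQD symptoms that keep deteriorating, poor compliance (under 80% of product used, or more than two visits missed), and the patient's own choice. The section does not mention outcome collection after withdrawal, and no other section does.
- **Statistical analysis:** the main primary analysis uses the "intention-to-treat data set, where the missing values will not be imputed". Users of unscheduled medication stay in their randomised group; withdrawn patients are not mentioned. The treatment effect is assessed by "comparing the mean between-group differences of the continuous endpoints with a normal distribution using the independent" t test, with Mann-Whitney for skewed variables. One of four sensitivity analyses is "imputing missing data using various methods dependent on the proportion and distribution of the missing data". The other three use the per-protocol set, exclude patients who learn their allocation, or exclude users of unscheduled medication.

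**The concern.** One withdrawal rule is triggered by worsening of the symptoms that the primary outcome measures. Two others, progression with restarted therapy and recurrent surgical complications, plausibly go with worse symptoms. The adherence rule depends on what patients do after randomisation. Because withdrawal is from the trial, a patient who meets a rule is likely to have no score at later visits. A t test on observed scores without imputation then omits that patient, whatever the analysis set is called.

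Randomisation makes the groups comparable as allocated. It does not make the patients who remain comparable if the arms lose different numbers or kinds of patient. What is at stake is the validity of the primary estimate: a real effect could be diluted, or an apparent one produced. A later statistical analysis plan can change the model, but it cannot supply scores that were never taken.

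**Working it through.** **1. The plan's own sample size.** Inputs from Sample size estimation: "we assume an α of 0.05, a 1 –β of 0.80", "a between-group difference in primary outcome (total SQD scale score) δ of 8.0", SD 14.5 and dropout 20%. Sidedness is not stated; two-sided is assumed.

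n per arm = 2 × [(1.960 + 0.842) × 14.5 / 8]² = 51.6, rounded up to 52. Then 52 / (1 − 0.20) = 65 per arm, 130 in total. This matches the plan. (One-sided gives 41, inflated to 52 per arm, which does not match.)

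Power at a difference of 8:
- 52 scored per arm: SE = 14.5 × √(2/52) = 2.84, power 80%.
- 65 scored per arm: SE = 14.5 × √(2/65) = 2.54, power 88%.

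The 20% allowance restores numbers after random loss. It does nothing about bias from selective loss.

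**2. A true difference of 8 and one common deterioration rule.** Assumptions, not document figures: change scores are normal with SD 14.5 in each arm (positive = worse), with mean 0 on placebo and −8 on HGMX. A patient whose change exceeds a cut c, measured from the placebo mean, is withdrawn and unscored. There is no other loss. With a = (c − μ)/14.5, the fraction lost is 1 − Φ(a), and the mean of those who remain is μ − 14.5 × φ(a)/Φ(a).

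At c = 15:
- Placebo: a = 1.034, 15.0% lost, remaining mean −3.99.
- HGMX: a = 1.586, 5.6% lost, remaining mean −9.74.
- Expected observed difference: 9.74 − 3.99 = 5.75, which is 28% below 8. The SE is 2.27 (using the reduced SDs and numbers), so power is about 72%.

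| Cut (points above placebo mean) | Lost, placebo | Lost, HGMX | Expected difference | Power |
|---|---|---|---|---|
| 10 | 24.5% | 10.7% | 5.0 | 62% |
| 15 | 15.0% | 5.6% | 5.8 | 72% |
| 20 | 8.4% | 2.7% | 6.5 | 79% |
| 25 | 4.2% | 1.1% | 7.1 | 83% |
| 30 | 1.9% | 0.4% | 7.5 | 86% |

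Here the rule removes more placebo patients, and the bias runs towards no effect.

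**3. No true difference.** Both arms have mean 0 and SD 14.5, and the worst-changing fraction p is lost. The remaining mean is −14.5 × φ(z)/(1 − p), where z is the upper-p normal quantile.

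- Equal loss, 20% in each arm: both means are −5.07, so the difference is 0. Simulated type I error was about 0.05 (65 randomised per arm, 10,000 runs).
- 25% lost on HGMX (mean −6.14) against 15% on placebo (mean −3.98): a spurious 2.2 points favouring HGMX, with type I error about 0.16.

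**4. Dependence on the visit.** Only three post-baseline visits (weeks 2, 4 and 8) fall by week 8, so the missed-visits rule could by then apply only to someone who missed all three. Progression, deterioration and poor adherence have more time to accumulate by week 104. The problem is likely to be smaller at early visits and larger at late ones.

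**The case against.** The strongest reply is that the withdrawal rules are the same in both arms and that clinicians, patients and assessors are blinded, so nothing removes patients unequally by design. This stands as a limit on what can be claimed. A reader might infer that the primary result is bound to be biased, or that an unimputed t test is valid only if data are missing completely at random. The documents do not support that: with no effect and equal withdrawal, the check above shows no bias and a type I error near 0.05. But if HGMX works as the sponsor hypothesises, a common deterioration rule will tend to remove more placebo patients, so identical rules do not give identical losses.

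The magnitude also rests on an assumed cut. If placebo patients improve on average, a rule defined from each patient's own baseline lies further out than the same cut above the placebo mean, and the shrinkage is small: 7.5 instead of 8 at a cut of 30. Against the planned 80%, power falls clearly short only at cuts of 10 and 15. The comparison flatters the lenient cuts, however, because the table allows for no other dropout.

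A reader might also take the 20% dropout figure to mean that up to a fifth of patients would be lost for outcome-related reasons. It is a sample-size allowance for all dropout, neither a cap nor an estimate of that kind of loss. Nor does more non-adherence on HGMX favour HGMX by itself; it does so only if the non-adherent patients fare worse.

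Finally, imputation is already listed as a sensitivity analysis, and its detail may properly sit in an analysis plan that is not shown. The open choice of method is therefore not counted as a separate fault. It does not answer the point either, because the primary result is unchanged by it and it cannot recover uncollected scores.

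**Conclusion.** The point holds as a material risk of bias, not as a demonstrated one. As written, the plan makes missing primary scores depend on the outcome, on prognosis and on adherence, and then compares the scores that remain under an intention-to-treat label. Nothing else in the article repairs this.

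Under the assumptions stated, a real 8-point effect would appear as about 5.0 to 7.5 points, with power between about 62% and 86%, against 80% planned after the dropout allowance and 88% if all 65 per arm are scored. With no effect, the error ranges from nothing (equal loss) to 2.2 points favouring HGMX (25% against 15% of the worst patients lost). The direction cannot be known in advance. The figures rest on normal change scores, withdrawal of the worst-changing patients, thresholds that the protocol does not give, and no scoring after withdrawal. It should be corrected before the primary analysis, and soon, because the follow-up part is useful only while patients can still be seen.

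**What to change.** (a) In Compliance and withdrawal, separate stopping the product from leaving the trial. Leave the product-stopping rules as they are. State that every randomised patient continues to be assessed on schedule to week 104 (SQD scale, SF-36, ECOG, weight and BMI, progression) unless consent is withdrawn.

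(b) In Statistical analysis, replace the unimputed t test as the primary analysis with a likelihood-based repeated-measures model containing baseline score, visit, arm and arm-by-visit, fitted to all observed visits of all randomised patients. Scores recorded before withdrawal, which often carry the deterioration that led to it, then inform the estimate. Support it with one prespecified sensitivity analysis for data missing not at random among patients who left for deterioration or progression; its detail can sit in the analysis plan.

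Cost: a protocol amendment, and further visits for withdrawn patients with the examinations and the 100-yuan travel allowance that the protocol provides at each visit. The Discussion expects most patients to return for regular postoperative follow-up with their attending physicians. That helps contact, but it is not the same as SQD scoring on the trial schedule. Recruitment began in May 2017 and 80 of the planned 130 patients were enrolled at submission, so scores from patients already withdrawn may not be recoverable.

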### Interventions and concomitant treatments

Eligible patients will receive either 30 g/day HGMX or 30 g/day placebo taken orally for 2 years. Every 30 g of HGMX contains 10.1 g of herbal materials. The placebo consists of early rice and oats and is identical to HGMX in terms of preparation, packaging, labeling, and color but is slightly different in taste and smell; according to our simulation test, the two treatments should be impossible to distinguish. The test samples will be distributed to patients once per month. Other Chinese herbal medicines and Western drugs to treat gastrointestinal symptoms (e.g., proton pump inhibitors, prokinetics) are prohibited. The patients will be asked to sign an integrity commitment; they should truthfully report whether they used a treatment outside the regimen at any time. This information will be recorded and used for sensitivity analyses.

Both groups will undergo surveillance of gastric cancer according to the Japanese Gastric Cancer Treatment Guidelines 2014 [4] and continuous concomitant care for other comorbidities (such as hypertension, diabetes mellitus, and osteoarthritis) during the study follow-up period. Concomitant treatments will be recorded at each visit.

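### Sensitivity analysis (4) excludes patients on a post-randomisation event that symptoms plausibly drive; it is a poor robustness check and should be replaced by one that keeps all randomised patients

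*Protocol article*

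**What the plan says.** Under Interventions and concomitant treatments, the article prohibits other Chinese herbal medicines and Western drugs for gastrointestinal symptoms. Patients undertake to report any treatment outside the regimen, and "This information will be recorded and used for sensitivity analyses".

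Under Statistical analysis, the main primary analysis is intention-to-treat without imputation, and "the patients who took unscheduled medications will be kept in their original group". Four sensitivity analyses are to test the robustness of the main result. The last is "4) excluding patients who took unscheduled medications". The term for unscheduled medication is not defined there; the prohibited treatments are the natural reading.

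The article gives no expected rate of use, overall or by arm, and no size for the effect of such treatment on the score. The Discussion expects the need for extra medicine to be infrequent, because only patients with ECOG 1 or lower enter.

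**The concern.** Patients enter because they have SQD symptoms, most of them gastrointestinal, and are then barred from other treatment for those symptoms. Those who take such treatment anyway are likely to be those who feel worst. Use is then partly a consequence of the primary outcome, and excluding users selects on that outcome after randomisation. If HGMX lowers symptoms, fewer HGMX patients reach the point of taking something else, so the exclusion would thin out the placebo arm's worst patients more than the HGMX arm's.

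What is at stake is how the robustness check is read. A real effect could look fragile because the check is biased towards no effect. More basically, a difference between (4) and the main result could not be interpreted, because the two do not estimate the same quantity and (4) has no clear target of its own.

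**Working it through.** **1. The plan's own figure.** The inputs come from Sample size estimation: "a between-group difference in primary outcome (total SQD scale score) δ of 8.0", with SD 14.5, 5% significance, 80% power and 20% dropout. Two-sided, n = 2 × (1.96 + 0.84)² × 14.5² / 8² = 51.6, so 52 per arm; 52 / 0.8 = 65 per arm, 130 in total. This matches the article. (One-sided gives 41, then 52 per arm, 104 in total, and does not match.) So 8 and 14.5 are used below.

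**2. How much of the score is gastrointestinal.** Maxima from the scoring rules under Primary outcome, with main symptoms counted twice:
- Items 1–2: 2 × 15 × 2 = 60
- Item 5: 11 × 2 = 22
- Item 6: 12 × 2 = 24
- Items 7–9: 3 × 15 = 45
- Items 10–12: 3 × 12 = 36
- Item 13: 9
- Item 14: 12

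These sum to 208. The rest (items 3–4: 48; items 15–17: 36) brings the total to 292, the stated maximum. Gastrointestinal items therefore supply 208/292 = 71%. The symptoms that would prompt a prohibited drug are largely the score itself.

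**3. Effect of excluding users.** Assumptions not in the documents: 20% use on placebo, and a correlation ρ between the propensity to use and the score. Without other treatment, let the change be N(0, 14.5²) on placebo and N(−8, 14.5²) on HGMX, with higher worse and no missing data. A patient uses other treatment when a latent normal propensity exceeds c₀ = 0.8416 (20% on placebo). On HGMX the threshold is in effect c₁ = 0.8416 + ρ × 8/14.5. With λ(c) = φ(c)/Φ(c) and R the points by which other treatment lowers the score:
- Use on HGMX = 1 − Φ(c₁)
- Exclusion estimate = 8 − 14.5ρ[λ(c₀) − λ(c₁)], where λ(c₀) = 0.350
- Main estimate = 8 − R × (0.20 − use on HGMX)

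| ρ | c₁ | Use on HGMX | λ(c₁) | Exclusion | Main, R = 8 | Main, R = 20 |
|---|---|---|---|---|---|---|
| 0 | 0.842 | 20.0% | 0.350 | 8.0 | 8.0 | 8.0 |
| 0.3 | 1.007 | 15.7% | 0.285 | 7.7 | 7.7 | 7.1 |
| 0.5 | 1.118 | 13.2% | 0.246 | 7.2 | 7.5 | 6.6 |
| 0.8 | 1.283 | 10.0% | 0.195 | 6.2 | 7.2 | 6.0 |

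For ρ = 0.5: 8 − 14.5 × 0.5 × (0.350 − 0.246) = 8 − 0.75 = 7.25. Exclusion thus loses 0.3 to 1.8 points over ρ = 0.3 to 0.8. In a variant where use follows scores already observed, which is closer to how patients behave, exclusion gives 7.8 down to 6.4, a loss of 0.2 to 1.6. With placebo use between 10% and 30%, and ρ between 0 and 0.8, the model above gives 5.7 to 8.0.

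**4. No effect of HGMX.** Then c₁ = c₀, use is equal between arms, the bracket is zero and neither analysis is biased.

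**5. Which analysis is closer?**
- Target: the effect regardless of other treatment. The main analysis is on target in this model. Exclusion differs from it by −2.3 to +0.8 points over the grid and is never closer.
- Target: the effect without other treatment (8.0). Over 36 settings (use 10, 20, 30%; ρ 0.3, 0.5, 0.8; R 0, 8, 14.5, 20), exclusion is further in 18, the main analysis in 16, and 2 tie. Nine of the 18 have R = 0, where the other treatment does nothing to the score.

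**6. Power.** With power = Φ(8 / (14.5 × √(2/n)) − 1.96), dropping 10%, 20% or 30% of 52 per arm lowers it from 80% to 76%, 71% or 65%, even if the effect stays at 8.

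**7. The alternative.** If use depends on scores already observed, the regression of later on earlier scores is the same in users and non-users of an arm, so imputing by arm from earlier scores is unbiased for the effect without other treatment. In the variant in step 3 this recovered 7.9 to 8.05 in every setting.

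**The case against.** Analysis (4) decides nothing. The main analysis keeps these patients, the article presents both side by side, and the Discussion expects extra medicine to be infrequent. If use is rare or weakly tied to symptoms, the distortion is a few tenths of a point. If HGMX works, the bias runs towards no effect, so a positive result that survives (4) is if anything conservative. Details of imputation may also sit in an analysis plan that is not shown. All of this stands as a limit on the size of the point. It does not rescue the method, because the exclusion itself is stated in the article and has no clear target.

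A reader might infer more than the documents support:
- *That (4) is further from the truth than the main analysis.* This is secure only for the effect regardless of other treatment; for the effect without it, step 5 shows the order going either way.
- *That a quarter to a third of the effect is lost.* Exclusion estimates of 5.3 to 6.0 at 20% use need use to be almost determined by symptoms (correlation about 0.85 to 1). At 0.3 to 0.5 the loss is about 4% to 9%.
- *That the main analysis wrongly credits placebo with the benefit of other drugs.* For the effect regardless of other treatment, that is what it should count.
- *That exclusion could flatter HGMX.* This needs HGMX to increase use of other treatment, for which the documents give no basis.

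**Conclusion.** The point holds as a cheap improvement to a secondary analysis. Analysis (4) selects on a post-randomisation event that is plausibly related to the outcome. If HGMX works and symptoms drive use, it is biased towards no effect, by about 0.2 to 1.6 of the planned 8 points at an assumed 20% placebo use. If HGMX has no effect, or use is unrelated to symptoms, there is no bias. The rate of use, its dependence on symptoms and the size of any effect of other treatment are all assumptions, so no single corrected figure follows from the documents. The main result does not depend on (4). The calculations also leave out missing data and the withdrawal of patients whose SQD symptoms keep deteriorating (Compliance and withdrawal), so the main analysis is not a perfect reference either.

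**What to change.** Replace sensitivity analysis (4) with one that:
- keeps all randomised patients in their arms;
- sets SQD scores after first use of a prohibited treatment to missing and multiply imputes them, by arm, from the patient's earlier scores;
- is labelled as estimating the effect without other treatment, with the missing-at-random assumption stated.

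Define unscheduled medication by reference to the prohibited treatments, and report the number and proportion of users by arm. A more conservative imputation is optional. The intention-to-treat main analysis stays as it is.

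Cost: analysis wording and slightly more programming. Treatment outside the regimen is already to be reported and concomitant treatment recorded at each visit, so no new data or patients are needed. The price is reliance on missing at random: if use responds to symptoms that the earlier scores do not capture, some bias remains.

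### Secondary outcomes, including progression-free survival, are assigned to the per-protocol set with no intention-to-treat analysis stated, although the withdrawal reasons are related to those outcomes

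*Protocol article*

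**What the plan says.** The Statistical analysis section of the protocol article treats the two classes of efficacy outcome differently. For the primary outcome, "The main primary outcome analysis will be based on the intention-to-treat data set", without imputation, and the per-protocol set appears only as one of four sensitivity analyses. For the rest, "The analysis of secondary outcomes will be based on the per protocol data set", again without imputation. No other set is named for them.

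The Secondary outcomes section lists SF-36 quality of life, ECOG performance status, body weight and body mass index, and PFS. Under Study visits and outcome assessments, at weeks 8, 26, 52, 78 and 104 "laboratory examinations and electrocardiograms will be performed, and cancer progression will be assessed".

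The Compliance and withdrawal section withdraws patients for progression with a restart of radiotherapy or chemotherapy, recurrent surgical complications, continuing worsening of symptoms, use of under 80% of the product or more than two missed visits, and at the patient's own wish. The article does not define the per-protocol set. It also does not say whether withdrawn patients are followed for progression.

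The Sample size estimation section calls the trial a superiority trial.

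**The concern.** Whether a patient belongs to a per-protocol set is decided after randomisation. Several withdrawal reasons here are close to the secondary outcomes. Progression with restarted therapy follows a PFS event. Continuing symptom deterioration plausibly goes with worse quality of life, performance status and weight. Low product use and missed visits may differ by arm, since the Interventions section says the placebo differs slightly in taste and smell (while reporting a test in which the two could not be told apart). If such patients are left out, the arms compared are no longer those formed by randomisation.

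Two uses of these results give the choice weight. The Discussion says the trial aims to clarify whether the product improves prognosis, and PFS is the listed outcome that bears on this most directly. The second criterion for discontinuing the trial under Data collection and monitoring refers to significance on any outcome up to week 52. As worded, that takes in the secondary outcomes.

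**Working it through.** **1. The plan's own figure.** Inputs from Sample size estimation: α 0.05, "a 1 –β of 0.80", "a between-group difference in primary outcome (total SQD scale score) δ of 8.0", SD 14.5 and 20% dropout.

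- n per arm = 2 × (1.96 + 0.8416)² × 14.5² / 8.0² = 51.6, rounded up to 52.
- Inflated for dropout: 52 / 0.80 = 65 per arm, 130 in total.

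The figure reproduces with a two-sided α and is not in dispute. It concerns the primary outcome. The article gives no event number, hazard ratio or power for PFS.

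**2. How many patients might leave the set.** 0.20 × 130 = 26. This holds only if the allowance is fully used and every dropout falls outside the per-protocol set. The article states no per-protocol exclusion rate.

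**3. Can exclusion create a difference where none exists?** All rates below are assumptions; none is in the documents. True 2-year progression risk is 30% in both arms.

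*Exclusion for non-compliance.* Suppose 20% of the active arm and 10% of the placebo arm are excluded, with 50% progression among those excluded.

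- Active: (0.30 − 0.20 × 0.50) / 0.80 = 25.0%.
- Placebo: (0.30 − 0.10 × 0.50) / 0.90 = 27.8%.
- The gap is 2.8 points. With 52 and 58.5 patients its standard error is √(0.25 × 0.75/52 + 0.278 × 0.722/58.5) = 8.4 points, so the bias is about one third of a standard error.

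*Exclusion of progressors.* If a share x of progressors leaves the set, the apparent risk is 0.30(1 − x) / (1 − 0.30x). The apparent hazard ratio is ln(1 − active risk) / ln(1 − placebo risk).

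| Progressors excluded, placebo / active | Apparent risk, placebo / active | Apparent hazard ratio |
|---|---|---|
| 50% / 50% | 17.6% / 17.6% | 1.00 |
| 50% / 70% | 17.6% / 11.4% | 0.62 |
| 40% / 80% | 20.5% / 7.9% | 0.36 |

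Reversing the arms reverses the direction. Equal exclusion leaves the null hazard ratio at 1.00, but the risk in each arm is still understated (17.6% against 30%).

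**4. Loss of information.** Assume 65 per arm, a true hazard ratio of 0.5 and 2-year control risks of 20%, 30% or 40%. Events with everyone kept = 65 × r + 65 × [1 − (1 − r)^0.5]. Power = Φ(½ × √events × |ln 0.5| − 1.96).

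| Control risk | Events, all kept (power) | Events, half of progressors lost (power) |
|---|---|---|
| 20% | 20 (34%) | 10 (19%) |
| 30% | 30 (48%) | 15 (27%) |
| 40% | 41 (60%) | 20 (35%) |

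The right-hand column assumes equal loss in both arms and an unchanged hazard ratio among those who remain. If all progressors were lost, no event would remain.

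**The case against.** The strongest reply is that the per-protocol set is undefined. Progression has already happened when it leads to withdrawal, and nothing in the article says that such a patient leaves the set or that the event goes uncounted. That stands. A reader might infer that PFS events will be lost, but the documents support only that they could be.

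A reader might also infer that PFS will be compared as a simple proportion or an uncensored time, because the tests named are a t test for "continuous endpoints with a normal distribution using the independent" comparison, Mann-Whitney, and for categorical variables "We will evaluate the between-group differences using Pearson’s chi-square test" or Fisher's exact test. The article does not assign any of these to PFS. A condensed article may leave the time-to-event method to the full protocol or analysis plan, so its absence is not an error, and this point does not rest on it.

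Nor is 26 a minimum number of exclusions. The 20% is an allowance used to size the primary analysis. An unimputed intention-to-treat comparison of quality of life or weight would also lose patients without data, so the loss due to the per-protocol choice itself is smaller than the number who drop out.

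Finally, the numerical scenarios rest on assumed rates, and the compliance scenario gives a bias that is small beside sampling error. The article promises only initial evidence, and its primary outcome is analysed by intention-to-treat.

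What the reply does not remove is the stated choice. The per-protocol set is named as the basis for every secondary outcome, and no other set is offered.

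**Conclusion.** The point holds as a criticism of the stated analysis set. In a superiority trial, the per-protocol set is the only one named for secondary outcomes, while patients are withdrawn for reasons related to those outcomes. Followed as written, the plan gives comparisons that randomisation may not protect.

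The size cannot be taken from the documents. Up to about 26 of 130 patients could be excluded, on the two conditions given above. With no true effect, the assumed scenarios run from no distortion of the hazard ratio under equal exclusion of progressors to an apparent value of 0.62 or 0.36 under unequal exclusion. There is no bias if exclusion is equal in the arms and unrelated to outcome. These figures show that bias can arise, not how large it would be here. Loss of PFS events is a risk that depends on a definition the article does not give.

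**What to change.** - Make all randomised patients, as assigned, the main analysis set for every secondary outcome, and keep per-protocol as supportive.
- For PFS, state that a progression leading to withdrawal counts as an event. Analyse time from randomisation with a method that handles censoring: Kaplan-Meier curves, a log-rank test and a Cox hazard ratio.
- Where consent allows, use routine cancer surveillance data to week 104 for withdrawn patients. The Interventions section already provides guideline surveillance in both arms, and the Discussion expects most patients to return for regular follow-up.

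The clinical withdrawal rule need not change, and N = 130 is unaffected. The cost is a change of wording in the protocol and analysis plan and some added data collection. Consent needs checking, because 80 patients were already enrolled when the article was submitted and patients may withdraw for any reason. Including patients who stopped the product may also dilute the estimated effect; the supportive per-protocol analysis would show the result among those who stayed on protocol.
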